### Data Collection, Measurements and Analysis Quantitative component

#### Primary outcome

HbA1c will be collected as a routine clinical measurement every third month, which is a standard practice. The capillary blood samples for HbA1c from both hospitals are being analysed at the same department of clinical biochemistry using Variant Analysis Mode, TOSOH Automated Glycohaemoglobin Analyzer HLC-723 G8 (normal range 4.3% - 5.8%).

#### Secondary outcome a

Danish versions of 6 scales were compiled in one questionnaire (Table 4). The questionnaires will be completed by the adolescents at the outpatient clinics and placed in a closed envelope before being returned to the personal HCPs at the following timepoints: 1) baseline before randomisation, 2) after the end of the intervention/control period (8-12 months), and 3) after a 6-month follow-up period (ranging between 14 and 18 months from the time of entry into the trial).

**Table 4 T4:** Adolescent measures and outcome

**Scales**	**Outcome**	**Ranging**	**Examples**	**Scores**
The Perceived Competence Scale (PCD) 5-item	Experience of own competence	Ranging from 1 (strongly disagree) to 7 (strongly agree)	*"I feel confident in my ability to manage my diabetes"*	Produces a total sum score from 5- 35. A high sum score represents a high level of perceived competence

The Health-Care Climate Questionnaire (HCCQ) 5 -item	Perceptions of autonomy support from HCP	Ranging from 1 (strongly disagree) to 7 (strongly agree)	*"I feel that my HCPs have provided me choices and options about handling my diabetes"*	Produces a total sum score from 5-35. A high sum score represents a high level of perceived autonomy support

The Treatment Self-Regulation Questionnaire (TSRQ) 21-item Consists of 3 subscales	The degree in which patients' behaviour is self-determined	Ranging from 1 (strongly disagree) to 7 (strongly agree)	*(I) Autonomous; "It's exciting to try to keep my blood sugar in a healthy range"* *(II) Controlled; "I want my HCP to think I am a good patient"* (III) A-motivated; "I do not know why I do try - I will not bee successful"	Produces sum scores for each of three subscales, Autonomous from 8-56, Controlled 9-63, Amotivated 4-28. High sum scores indicate high levels of autonomy, controlled or amotivated behaviour. A Relative Autonomy Index is calculates by subtracting the controlled scores from the autonomous scores. The higher relative autonomy index the higher is motivation based on autonomy compared to control

The Problem Areas In Diabetes scale (PAID) 20-item	Perception of current emotional burden of diabetes related issues	Ranging from 0 (not a problem) to 4 (serious problem)	*"Feelings of guilt or anxiety when you get off track with your diabetes management"*	Produces a total score from 0-100 by summing up and multiplying this sum by 1.25. Higher scores indicate greater emotional distress. Cut points: ≥30 elevated distress ≥40 serious distress

The Perception of Parents Scale (POPS) 26-item Consists of 2 sub-scales, mothers & fathers	Perception of autonomy support and involvement from parents	Ranging from 1 (not at all true) to 7 (very true)	*(I) Mother/Father Autonomy Support;* *"My mother/father allows me to decide things for myself"* (II)Mother/Father Involvement; "My mother/father finds time to talk with me"	Produces a total sum score from 13-91 in each subscale. High sum scores represent a high level of mother/father autonomy support/involvement

The WHO5 Well-Being Index 5-item	Emotional Well-being	Ranging from 0 (not present) to 5 (constantly present).	*"I have felt cheerful and in* *good spirits for the last* *two weeks"*	Produces a total score from 0-100 by summing up and multiplying a sum score by 4. Higher scores indicate greater emotional distress. Cut points: < 50 poor emotional well-being ≤ 28 indicate depression

The scales included the following:

▪ Perceived competence for diabetes management (PCD), assessing patients' experiences of feeling able to manage their diabetes successfully [65]

▪ Health Care Climate Questionnaire (HCCQ) assessing the degree to which patients believed their HCPs to be autonomy-supportive versus controlling in providing general treatment [65]

▪ Treatment Self-Regulation Questionnaire (TSRQ) assessing the motivation for diabetes management and the degree to which behaviours tended to be self-determined. The TRSQ consists of three subscales; (I) Autonomous, (II) Controlled, (III) A-motivated [66]

▪ Problem Areas In Diabetes (PAID) assessing diabetes-related distress including a wide range of feelings related to living with diabetes and its treatment, including guilt, anger, depressed mood and fear [67]

▪ The Perception of Parents Scale (POPS) [68] assessing adolescents' perceptions of their parents' autonomy support and involvement

▪ WHO-5 Well-being Index capturing emotional well-being in the last two weeks (WHO-5) [69].

The scales were translated and harmonised in accordance with recommended guidelines [70]. Internal consistency was measured for all 6 scales and proved to be good. Cronbach's α ranged from 0.76-0.94 for the Danish versions of the HCCQ, PCD and TSRQ for adults, [47]; the Cronbach's α for the English version for adolescents of the WHO5 was 0.82 [69], 0.96 for the PAID [71] and 0.88 for the POPS Autonomy support from mothers and fathers [58]. Face validity of the Danish versions was tested in 8 adolescents between 13 and 18 years of age with type 1 diabetes.

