### Analysis

To meet Objective 2 and test if GSD-Y effectively reduces HbA1c and improves life skills in adolescents with type 1 diabetes, we will analyse HbA1c and quantitative data from the questionnaires using PAWS Statistics18 for Windows (SPSS Chicago, IL, USA). Statistical analyses will include frequency, mean, standard deviation and confidence intervals. Comparisons of primary and secondary outcomes for the two groups will be conducted comparing data at baseline, at the end of the study, and after a 6-month follow-up period using appropriate parametric tests for variables fulfilling the normal distribution criteria or appropriate non-parametric tests for variables not fulfilling the normal distribution criteria. A Bonferroni correction for multiple testing will be performed.

Improvement of life skills will be defined as increases in HCCQ-scores, TSRQ-scores on autonomy or in relative autonomy index (formed by subtracting TSRQ-scores on control from TSRQ-scores on autonomy), PCD, POPS, WHO-5 and frequency of SMBG per week, and decreases in TSRQ-scores on amotivation, PAID scores and HbA1c. Differences within the GSD-Y group and between the GSD-Y group and the control group will be calculated at the end of the intervention (8-12 months) and after a 6-month follow-up period.

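### The Relative Autonomy Index subtracts a 9-item sum from an 8-item sum, so equal per-item rises in both subscales slightly lower it

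*Protocol article*

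**What the plan says.** Table 4, under Secondary outcome a, introduces the scale as "The Treatment Self-Regulation Questionnaire (TSRQ) 21-item" with answers "Ranging from 1 (strongly disagree) to 7 (strongly agree". On scoring it says "Produces sum scores for each of three subscales" and gives the ranges "Autonomous from 8-56, Controlled 9-63, Amotivated 4-28". The index follows directly: "A Relative Autonomy Index is calculates by subtracting the controlled scores from the autonomous scores". Its meaning is then given: "The higher relative autonomy index the higher is motivation based on autonomy compared to control".

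The Analysis section uses the same construction, "formed by subtracting TSRQ-scores on control from TSRQ-scores on autonomy". It accepts a rise either in the autonomy subscale or in this index as an improvement in life skills. It plans comparisons both within the GSD-Y group and between the two groups, at the end of the intervention and after the 6-month follow-up.

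Neither place mentions item means, weights or rescaling. Neither gives a meaning to an index of zero or sets a cut point for it.

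**The concern.** A difference score compares like with like only if its two parts are on the same scale. Here one part is a sum of 8 items and the other a sum of 9, so a given shift in average answer moves the controlled part further than the autonomous part.

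If adolescents endorse both kinds of motivation more strongly by the same amount per item, the index falls, and the plan reads that as movement away from autonomy. The two alternative TSRQ criteria in the Analysis section can then point in opposite directions for the same respondent purely because of item counts.

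The scoring rule is specific and is stated twice, so it is not a detail left open for a later document. What is at stake is the meaning of a change in one component of a secondary outcome. HbA1c and the sample size are not affected.

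**Working it through.** **Inputs (Table 4):** item scale 1 to 7; 21 items; sum ranges 8–56 (autonomous), 9–63 (controlled) and 4–28 (amotivated); index = autonomous sum − controlled sum.

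**Step 1: reproduce the stated ranges.** A subscale of k items scored 1–7 runs from k to 7k.
- k = 8 gives 8–56, k = 9 gives 9–63 and k = 4 gives 4–28.
- 8 + 9 + 4 = 21, the stated total.

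The ranges are internally consistent, and the item counts follow from them.

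**Step 2: write the index in item means.** With autonomous item mean a and controlled item mean c:

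index = 8a − 9c

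- Relative weight of c to a: 9/8 = 1.125, i.e. 12.5% more per item-mean point.
- Minimum 8 − 63 = −55; maximum 56 − 9 = +47; span 47 − (−55) = 102; midpoint −4.

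**Step 3: equal item means.** If a = c = m, the index is 8m − 9m = −m: −1 when every answer is 1, −4 when every answer is 4, −7 when every answer is 7. An index of 0 needs a = 1.125c, for example 4.5 against 4.0 (sums 36 and 36).

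**Step 4: equal rises.**
- One point more on every item of both subscales: +8 − 9 = −1. The autonomy subscale alone records +8 for the same respondent.
- Moving every answer from 1 to 7, the largest possible common shift: −7 − (−1) = −6.
- Equal rises in the raw sums, for example +8 in each: +8 − 8 = 0.

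**Step 5: ranking against the stated interpretation,** using attainable whole-number answers.

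| Respondent | Autonomous sum (mean) | Controlled sum (mean) | Index as written | Difference of means |
|---|---|---|---|---|
| A, all answers 2 | 16 (2.00) | 18 (2.00) | −2 | 0 |
| B | 56 (7.00) | 60 (6.67) | −4 | +0.33 |

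B favours autonomous over controlled motivation per item and A is neutral, yet B has the lower index.

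**Step 6: when a change has the wrong sign.** If both means rise, the index falls although a has risen more than c whenever the rise in c lies between 8/9 of the rise in a and the rise in a itself. Example: a up 1.0 and c up 0.9 gives 8.0 − 8.1 = −0.1, while the difference of means gives +0.1. The zone is narrow.

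**Step 7: after rescaling.** Autonomous sum/8 minus controlled sum/9 runs from 1 − 7 = −6 to 7 − 1 = +6. It is 0 whenever the item means are equal, and equal per-item rises leave it unchanged.

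**The case against.** The strongest reply is that the plan defines motivation by sum scores, and in those units equal rises cancel. That is correct, so the point must be put per item.

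A reader might infer from the −m result that the index misclassifies balanced adolescents. The documents do not support that. They give cut points for PAID and WHO-5 but none for this index, and only changes and differences are analysed. The displaced zero and the asymmetric range affect how a value is read, not any planned test.

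A reader might also infer that the scoring biases the trial against GSD-Y. That is not supported either. Under the null the randomised between-group comparison stays valid, and a shift common to both arms cancels. The theoretical framework describes an intervention meant to foster autonomous motivation and reduce controlling behaviour; if controlled scores fall, the heavier weight on that subscale works slightly in favour of GSD-Y. There is no general direction.

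The size is also modest. A half-point shift on every item in one arm only moves the index by 0.5. The documents give no standard deviation for the index. Assuming 8 to 15 points, 0.5 is about 0.03 to 0.06 SD, against the 1.0/1.3 ≈ 0.77 SD on which the HbA1c sample size rests. The autonomy subscale is also a criterion in its own right, so a reader can see its change directly.

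Finally, subtracting sums weights every item equally, while subtracting means weights each subscale equally, and neither equalises the influence of subscale variances. Whether sums are the instrument's prescribed scoring cannot be checked from this document.

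These arguments limit the importance of the point. They do not remove the mismatch: Table 4 interprets the index as autonomy compared with control, and the respondents in Step 5 show that the formula can order people the other way. The within-group comparison planned for GSD-Y also has no control arm to cancel a general shift in response level.

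**Conclusion.** The point holds in a limited form. As written, the index gives controlled motivation 12.5% more weight per item-mean point and falls by 1 for each scale point by which both subscales rise together, up to 6 points on a span of 102. It therefore distorts estimated change, within GSD-Y and between groups, when both kinds of motivation shift, and it can rank near-balanced respondents at different response levels against its stated meaning.

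The conclusion rests only on the item counts implied by Table 4 and on the subtraction being carried out on the sums, as both places describe. It is a small scoring defect in one component of a secondary outcome. It is worth correcting because the correction is simple and makes the index agree with its own definition.

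**What to change.** Before analysis, define the index as the autonomous item mean (sum/8) minus the controlled item mean (sum/9), range −6 to +6, and use the same wording in Table 4 and in the Analysis section. The subscale sum scores can stay as they are.

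This takes one line of scoring and two edits to the text, with no new data. It should be settled before results are seen, because a later change of scoring would be open to challenge. If comparability with earlier sum-scored work is wanted, report the sum-based index alongside and state its unequal item counts. The minor cost is two versions of one secondary score, so the plan should name the item-mean version as the one used to judge improvement.

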#### Secondary outcomes b and c

Regarding secondary outcomes b and c, a case report form will be completed at every outpatient visit by the adolescents' HCPs. Furthermore, demographic data will be collected at baseline, after the intervention/control period and at the 6-month follow-up.

### Analysis

To meet Objective 2 and test if GSD-Y effectively reduces HbA1c and improves life skills in adolescents with type 1 diabetes, we will analyse HbA1c and quantitative data from the questionnaires using PAWS Statistics18 for Windows (SPSS Chicago, IL, USA). Statistical analyses will include frequency, mean, standard deviation and confidence intervals. Comparisons of primary and secondary outcomes for the two groups will be conducted comparing data at baseline, at the end of the study, and after a 6-month follow-up period using appropriate parametric tests for variables fulfilling the normal distribution criteria or appropriate non-parametric tests for variables not fulfilling the normal distribution criteria. A Bonferroni correction for multiple testing will be performed.

Improvement of life skills will be defined as increases in HCCQ-scores, TSRQ-scores on autonomy or in relative autonomy index (formed by subtracting TSRQ-scores on control from TSRQ-scores on autonomy), PCD, POPS, WHO-5 and frequency of SMBG per week, and decreases in TSRQ-scores on amotivation, PAID scores and HbA1c. Differences within the GSD-Y group and between the GSD-Y group and the control group will be calculated at the end of the intervention (8-12 months) and after a 6-month follow-up period.

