### Setting

The study takes place at 2 paediatric outpatient clinics at 2 hospitals in the capital region of Denmark: Glostrup, with the largest diabetes outpatient clinic in Denmark (480 patients) and Hillerød, with the third largest diabetes outpatient clinic in Denmark (171 patients).

Two paediatric physicians, 5 paediatric diabetes nurses and 2 dieticians (HCP hereafter), trained and tested in using GSD-Y, will recruit adolescents with type 1 diabetes and conduct the GSD-Y intervention as part of their routine outpatient clinic visits.

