### Enrolment

#### Inclusion criteria

All adolescents aged 13-18 years who have had type 1 diabetes for more than one year will be invited to participate together with their parents if they meet the following criteria:

▪ HbA1c ≥ 8.0% at the last visit before entry into the study and

▪ Average HbA1c > 7.5% during the last year before entry into the study.

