### Randomisation

Adolescents and parents willing to participate and fulfilling the inclusion criteria will be randomised to either an intervention group (n = 34) (GSD-Y) or a control group (n = 34) (standard care), using stratified randomisation by the adolescent's usual HCP. Randomisation will be performed using sealed envelopes. Neither adolescents nor the HCPs can possibly be blinded to the study. The adolescents in the control group will be offered the GSD-Y intervention after the study has concluded (14-18 month wait-list design).

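### The HbA1c test and effect measure are left to an unstated normality criterion, with no stated covariate role for baseline HbA1c or usual HCP; one prespecified baseline-adjusted model would fix both and gain power

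*Protocol article*

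**What the plan says.** The Analysis section of the protocol article applies one rule to primary and secondary outcomes alike. Groups are compared "using appropriate parametric tests for variables fulfilling the normal distribution criteria or appropriate non-parametric tests" where normality does not hold, "comparing data at baseline, at the end of the study, and after a 6-month follow-up period". It adds that "Differences within the GSD-Y group and between the GSD-Y group and the control group will be calculated" at the end of the intervention and again at the 6-month follow-up. No normality criterion is given. Nor does it say whether the criterion applies per arm, per time point or to changes from baseline. No test or model is named for HbA1c.

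The Sample size calculation section is based on an absolute HbA1c difference of 1.0%, a standard deviation of the HbA1c value of 1.3%, power 0.8 and two-sided 0.05. It arrives at 26 per group and, allowing for 25% attrition, 68 in total.

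The Randomisation section allocates "using stratified randomisation by the adolescent's usual HCP". The Analysis section does not mention HCP. Under Data Collection, "HbA1c will be collected as a routine clinical measurement every third month", so serial values will be available for everyone.

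**The concern.** Two things are fixed badly for the primary outcome.

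- **The effect measure is not settled in advance.** The trial is sized on a difference in means. If the unstated criterion fails, a rank test replaces that comparison. The rule could also give one kind of test at the end of the intervention and another at follow-up.
- **Information already collected has no stated use.** Baseline HbA1c usually predicts later HbA1c, so adjusting for it reduces residual variance. Here it is listed only as a time point to compare. A stratification factor normally belongs in the analysis too, because stratifying removes between-stratum variation from the treatment contrast, while an unadjusted standard error still includes it.

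At stake is mainly precision, in a trial expecting about 51 evaluable adolescents, and a primary result whose form is known in advance.

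**Working it through.** **Inputs from the protocol article.** Difference 1.0; SD 1.3; two-sided 0.05; power 0.8; 26 per group; 68 recruited; attrition 25%. Evaluable: 68 × 0.75 = 51, taken as 25 and 26. The Bonferroni divisor is not stated, so everything below is at 0.05.

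**Assumptions, not in the article.** Correlation r between baseline and follow-up HbA1c in the enrolled sample: 0.3, 0.5, 0.6, 0.7. Number of HCP strata: 7, from the Setting section's "Two paediatric physicians, 5 paediatric diabetes nurses and 2 dieticians", leaving out the dieticians. Share of HbA1c variance due to HCP: 0, 10% or 20%.

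**Step 1: reproduce the stated size.** For an unadjusted two-sample comparison, n per group = 2 × [1.3 × (1.960 + 0.842) / 1.0]² = 26.5, which rounds up to 27 against the stated 26. Power at 26 per group is 0.79 (normal approximation) or 0.78 (noncentral t). A one-sided test would need 21. So the sizing matches a two-sided unadjusted comparison using the raw SD.

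**Step 2: unadjusted precision at 25 and 26.** Standard error = 1.3 × √(1/25 + 1/26) = 0.364. The 95% CI half-width is 2.01 × 0.364 = 0.73. Noncentrality is 1.0/0.364 = 2.75, giving power 0.77.

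**Step 3: adjust for baseline.** Residual SD = 1.3 × √(1 − r²), and the same steps give:

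| r (assumed) | Residual SD | Standard error | CI half-width | Power for 1.0 |
|---|---|---|---|---|
| unadjusted | 1.30 | 0.364 | 0.73 | 0.77 |
| 0.3 | 1.24 | 0.347 | 0.70 | 0.81 |
| 0.5 | 1.13 | 0.315 | 0.63 | 0.87 |
| 0.6 | 1.04 | 0.291 | 0.59 | 0.92 |
| 0.7 | 0.93 | 0.260 | 0.52 | 0.96 |

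**Step 4: allow for the entry cut.** Eligibility requires "HbA1c ≥ 8.0% at the last visit before entry into the study", which narrows the baseline range. If baseline were normal with mean 8.2 (assumed) and SD 1.3 and cut at 8.0, correlations of 0.5, 0.6 and 0.7 before selection would become about 0.34, 0.43 and 0.53 after it. Keeping SD 1.3, power is then about 0.82, 0.85 and 0.89. The lower half of the table is therefore the optimistic part.

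**Step 5: if the parametric test were on change scores.** The SD of change is 1.3 × √(2(1 − r)). Power is 0.62 at r = 0.3 and 0.77 at r = 0.5, the latter no better than ignoring baseline. So the open wording covers analyses of quite different efficiency.

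**Step 6: the HCP strata, by simulation.** With 7 strata, 25% random loss and no baseline term, adding HCP changes power from 0.767 to 0.750 if HCP explains nothing, and from 0.795 to 0.833 if it explains 20%. In the 20% case the type I error of the unadjusted test is 0.035, against 0.046 with HCP in the model. With ANCOVA at r = 0.5, 52 patients and HCP explaining 10%, adding HCP takes power from 0.88 to 0.90. The overall range is about −2 to +4 points.

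**Step 7: the normality rule, by simulation.** Settings: 52 patients, r = 0.5, and a Shapiro-Wilk check in each arm leading to a t-test or Mann-Whitney test.

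- The check rejected normality in about 10% of trials with normal data and 56–68% of trials with skewed data.
- The two tests gave different verdicts in 2–9% of trials.
- Type I error of the two-stage procedure was 0.04–0.06.
- Its power was 0.77–0.82, against 0.77–0.79 for the t-test alone and 0.87–0.88 for baseline-adjusted ANCOVA without an HCP term.

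**The case against.** The strongest reply is that this is a condensed article. It names no test, so its reference to parametric tests leaves room for ANCOVA or a mixed model, and baseline is among the data compared. Covariates are commonly left to an analysis plan, and an unadjusted sample size does not bind the analysis. All of that stands. A reader might infer that the plan fixes a simple two-group test and ignores baseline and strata, but the text does not say so. What the reply does not reach is the selection rule, which the article does state and which governs the primary outcome.

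Three other strong readings are tempting and should not be drawn.

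- **That the result is left to chance.** The simulated error rate stayed near nominal, and the two-stage procedure was no less powerful than the t-test. The article also promises means and confidence intervals whichever test is used. The problem is a test and effect measure that depend on the data, not an invalid test.
- **That the entry cut makes a rank test likely.** In the model of Step 4, truncated baseline values fail a Shapiro-Wilk check about 54% of the time at n = 26. The efficacy comparison uses follow-up values, though, and in the same model these fail only about 5–6% of the time, close to the nominal rate. The cut also applies to the last visit before entry, not necessarily to the baseline value itself.
- **That omitting the strata invalidates the test.** It makes the test slightly conservative if HCP matters and costs few power points. The number of strata is not given, and the randomisation sentence could mean that the HCP carries out the randomisation. Stratification by HCP is the natural reading, but not the only one.

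**Conclusion.** The point holds in a limited form. The Analysis section makes the primary HbA1c test, and with it the effect measure, depend on an unstated criterion, although the trial is sized on a mean difference. It gives baseline HbA1c no stated covariate role and does not mention HCP.

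The cost is precision rather than validity. Relative to the unadjusted comparison that the sizing implies, prespecified baseline adjustment would raise power for 1.0% by about 4 points at r = 0.3 (0.77 to 0.81), 10 points at r = 0.5 and 19 points at r = 0.7. The CI half-width would fall by about 0.03, 0.10 and 0.21 HbA1c points respectively. These figures assume an SD of 1.3, 51 evaluable adolescents, alpha 0.05 and a correlation that the document does not give. The direction of the gain holds at every value examined, but its size does not, and the lower end is plausible. Nearly all of the gain comes from baseline. The change is worth making, but the trial does not fail without it.

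**What to change.** For HbA1c, replace the normality-driven choice with one model named in advance:

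- ANCOVA of HbA1c on arm, baseline HbA1c and usual HCP, or a mixed model on the quarterly values with the same terms.
- HCP as a random effect, or clinic in its place if the HCP strata are too small for 68 adolescents.
- The adjusted mean difference with its 95% CI as the reported effect, on the same scale as the 1.0% used for sizing.
- Rank methods as a sensitivity analysis only.

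The Randomisation section should also say plainly that HCP is the stratification factor, if that is what is meant.

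The cost is wording. No new data are needed, since HbA1c is measured routinely and each adolescent's HCP is known. Statistically, the model spends one degree of freedom on baseline and, with 7 HCPs as fixed effects, 6 more. That costs about 1–2 power points if HCP explains nothing; a random effect costs less.

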**Methods/Design:**

Using a mixed methods design comprising a randomised controlled trial and a nested qualitative evaluation, we will recruit 68 adolescents age 13 - 18 years with type 1 diabetes (HbA1c > 8.0%) and their parents from 2 Danish hospitals and randomise into GSD-Y or control groups. During an 8-12 month period, the GSD-Y group will complete 8 outpatient GSD-Y visits, and the control group will completes an equal number of standard visits. The primary outcome is HbA1c. Secondary outcomes include the following: number of self-monitored blood glucose values and levels of autonomous motivation, involvement and autonomy support from parents, autonomy support from HCPs, perceived competence in managing diabetes, well-being, and diabetes-related problems. Primary and secondary outcomes will be evaluated within and between groups by comparing data from baseline, after completion of the visits, and again after a 6-month follow-up. To illustrate how GSD-Y influences glycaemic control and the development of life skills, 10-12 GSD-Y visits will be recorded during the intervention and analysed qualitatively together with individual interviews carried out after follow-up.

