### Sample size calculation

The size of the study was based on the primary outcome measure HbA1c. According to a power calculation, an absolute difference of 1.0% in HbA1c between the GSD-Y group and the control group (power 0.8; two-sided level of significance 0.05) could be detected with 26 patients in each group. This calculation was based on a standard deviation of the HbA1c value of 1.3% from a study of coping skills training [45]. To compensate for an attrition rate of 25%, we aimed to recruit 68 patients.

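### HbA1c is sized as one test at 0.05 but analysed at two times under a Bonferroni correction of unstated scope, so the 80% power does not hold for an individual HbA1c comparison

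*Protocol article*

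**What the plan says.** Under Endpoints, the primary outcome is HbA1c, with no time point attached. The Sample size calculation states that "The size of the study was based on the primary outcome measure HbA1c" and gives the target as "an absolute difference of 1.0% in HbA1c between the GSD-Y group and the control group (power 0.8; two-sided level of significance 0.05", which "could be detected with 26 patients in each group". It adds that "This calculation was based on a standard deviation of the HbA1c value of 1.3" (per cent HbA1c). Allowing for 25% attrition, the recruitment target is 68, randomised 34 and 34. No allowance for multiple testing appears there.

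The Analysis section compares the two groups on primary and secondary outcomes together, "comparing data at baseline, at the end of the study, and after a 6-month follow-up period", using parametric or non-parametric tests as appropriate. It then says "A Bonferroni correction for multiple testing will be performed". The number of tests, the family and the corrected level are not given, and HbA1c is not set apart. The following paragraph lists HbA1c beside the questionnaire scores in the definition of improved life skills. It places the between-group and within-group differences at two post-baseline times: the end of the intervention (8 to 12 months) and the 6-month follow-up. The Abstract agrees: "Primary and secondary outcomes will be evaluated within and between groups".

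**The concern.** The two sections do not describe the same test of the main question. One plans a single HbA1c test at 0.05. The other plans at least two between-group HbA1c tests and a correction that, read in sequence, applies to them too. If the correction is applied as written, a true 1.0% difference may be missed far more often than the design implies, and a null result would be hard to interpret.

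Dropping the correction from both HbA1c tests without naming a lead time point is no remedy. The chance of a false positive at one or other time would then be about 7% to 9%. Because the family is open, the threshold for the primary outcome could also be settled after the results are known.

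**Working it through.** **Inputs.** From the Sample size calculation: difference 1.0, SD 1.3, two-sided 0.05, power 0.80, 26 per group, 25% attrition, 68 recruited. From Randomisation: 34 per group. From Analysis: two post-baseline times. Evaluable number: 68 × 0.75 = 51, taken as 25 and 26.

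**Step 1: reproduce the planned size.** Normal approximation: n per group = 2 × SD² × (z₀.₉₇₅ + z₀.₈₀)² / difference² = 2 × 1.69 × (1.960 + 0.842)² = 26.5. This rounds up to 27, against the stated 26. Power with 26 per group is 0.79 by the normal approximation and 0.78 by t-test. A one-sided test would need 21. The plan's figure is therefore that of one two-sided test at 0.05, with no correction.

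**Step 2: power for one HbA1c comparison at corrected levels.** Two-sample t-test, 25 and 26 evaluable, 49 degrees of freedom. Noncentrality = 1.0 / (1.3 × √(1/25 + 1/26)) = 2.75.

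| Family | Level per test | Power |
|---|---|---|
| One test | 0.05 | 0.768 |
| HbA1c at 2 times | 0.05/2 = 0.025 | 0.668 |
| 10 measures × 2 times = 20 | 0.0025 | 0.343 |
| 11 measures × 2 times = 22 | 0.0023 | 0.332 |

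The last two rows rest on an assumed count. The measures listed in the Analysis section are HCCQ, TSRQ autonomous, the relative autonomy index, PCD, POPS, WHO-5, frequency of self-monitoring, TSRQ amotivation, PAID and HbA1c. That is 10, or 11 if POPS is counted separately for mother and father. Within-group tests are left out; counting one for each between-group test (44 tests) would lower the power to 0.256.

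**Step 3: size needed for 80% power per comparison (t-test).** At 0.025, 34 evaluable per group, so 68/0.75 = 90.7, or 91 recruited. At 0.0025, 53 per group, so 106/0.75 = 141.3, or 142 recruited. The plan recruits 68.

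**Step 4: a win at either time, two tests only.** Assume a true 1.0% difference at both times, each tested at 0.025, with 25 and 26 evaluable. By the bivariate normal approximation, the power to succeed at one time or the other is 0.84, 0.80 and 0.76 for assumed correlations of 0.5, 0.7 and 0.9. A t-test simulation gives 0.82, 0.78 and 0.74. These are close to the uncorrected single-test figures on the same two methods (0.78 normal, 0.77 t-test).

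**Step 5: no correction.** With both times tested at 0.05 and a win allowed at either, the false-positive rate is 9.1% at an assumed correlation of 0.5 and 7.0% at 0.9.

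**The case against.** The strongest reply is that the Analysis section states no corrected level for HbA1c. The only level printed for it is 0.05, which would fit a correction meant for the secondary outcomes alone. A condensed article may also leave the exact family to a fuller document. A reader might infer that the plan fixes two different levels for the same test. The text does not support that: it gives one level and a correction of open scope. What remains is that the correction directly follows a sentence naming primary and secondary outcomes together, and nothing takes HbA1c out.

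A reader might also infer that the trial has only about one-third power. That holds only if HbA1c is pooled with the questionnaires, and the 20 to 22 tests are counted from the list of measures, not stated. With two HbA1c tests and a win at either, Bonferroni costs little. Baseline adjustment or complete retention would also help: at 0.025 the power is 0.80 with an assumed baseline correlation of 0.5, and 0.81 with no attrition. At 20 tests these give only 0.50 and 0.52. The protocol states none of these conditions.

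Two further objections stand. The gap between 0.80 and 0.77 comes from rounding and the normal approximation, not from Bonferroni. And the wording does not establish that significance tests between groups at baseline are planned: the Abstract can be read as describing change from baseline, and the Analysis section places the calculated differences at the two later times.

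**Conclusion.** The concern holds as a mismatch whose cost depends on a family that the protocol leaves undefined. The planned size reproduces only as one two-sided HbA1c test at 0.05, whereas the analysis has two such comparisons under an unrestricted correction. If HbA1c is corrected at all, an individual comparison falls short of 80% power at the planned evaluable number: about 0.67 under the narrowest family and 0.33 to 0.34 under the assumed pooled one. These figures take the protocol's 1.0% difference, SD of 1.3% and 25% attrition, with an unadjusted t-test. The loss is serious under pooling. It is slight if only two HbA1c tests are corrected and success at either time counts, given equal effects at both times and the assumed correlations.

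**What to change.** Before outcomes are compared by group, name one HbA1c time point as the single confirmatory between-group test at two-sided 0.05. Which one is the sponsor's choice, since the protocol ranks neither; the end of the intervention is one example. Test the other time point second, in fixed sequence, at 0.05. Confine Bonferroni or Holm to the between-group secondary outcomes and state how many tests it spans.

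The cost is about two sentences in the Analysis section and no extra patients. The first HbA1c test then matches the sample size calculation, apart from the rounding noted above. The downside is that the second time point cannot be claimed as confirmatory if the first test fails.

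Alternatively, keep the correction on HbA1c, state the divisor and the rule for success, and restate the power at the corrected level. That means accepting the lower power or recruiting more patients: about 91 for 80% power per test with two tests.
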